##### Secondary outcome (compulsion duration)

EPCS-rated duration of observed compulsions (in seconds, summed across all sessions) will quantify compulsive behavior. We will fit two linear regression models with compulsion duration as the dependent variable to establish if there exist differences in how iTBS, cTBS, and sham conditions affect compulsion duration. Group indicators for these conditions (active vs sham) will be the primary model predictors. Given that the overall exposure duration naturally varies across patients and sessions, [36] relates to ERP outcomes, and can influence compulsion duration (i.e. longer exposures have more opportunity for compulsions), total exposure duration (in seconds) will be a covariate in the model.

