## Intervention description {11a}

Participants will receive 12 treatment sessions, delivered daily on consecutive weekdays. The first and twelfth sessions will be ERP orientation and relapse prevention sessions, respectively. Treatment sessions 2–11 will involve TMS immediately followed by ERP (Fig. 2). The number and timing of sessions was designed to ensure delivery of a full course of efficacious ERP [3, 4] alongside daily TMS, which is linked to long-lasting neural and behavioral change [30].

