### Strategies to improve adherence to interventions {11c}

Coil placement during TMS administration will be continually monitored using BrainSight (BrainSight 2.3.5, Rogue Research, Montreal, Quebec, Canada). All ERP sessions will be video recorded and 100% will be coded using the Exposure Process Coding System (6) to measure compulsions and therapist and patient adherence. Participant compliance with ERP assignments and in-session tasks will be tracked by the ERP therapist at each session.

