### Measure procedures

#### Exposure Process Coding System (EPCS)

EPCS [6, 36] is an observer-rated, microanalytic, time-stamped coding system that uses Noldus Observer software to capture in-session behaviors as they occur on video. EPCS measures the frequency and duration of youth compulsions during exposure tasks, along with codes measuring therapist behaviors (which serve as an index of treatment fidelity) and youth distress levels (youth-reported and observer-rated; which can index exposure learning). Bachelor’s degree-level study coders will code 80% of video-taped session data. Coders will be trained and monitored to prevent drift. Training will include background reading, group discussions, practice coding with feedback, and practice coding to criterion. Raters must attain reliability on practice videos (*k* > 0.80) before coding study videos. If coder drift is detected, re-training will occur and remaining study videos will not be coded until the reliability criterion is re-established. Ten percent of sessions will be double-coded to assess reliability.

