##### Primary outcome (compulsion duration)

Following procedures outlined for this outcome in Phase 1, a linear regression model will assess whether compulsion duration differs by treatment group. A linear regression model will also be used with the outcome of interest being the percent change in OCD symptom severity (C/YBOCS) pre- to post-treatment. The primary predictor will be a group indicator for sham vs active rTMS. Compulsion duration and its interaction with the group indicator will be included as potential mediators for the dependent variable. Total exposure duration will be a covariate in both analyses.

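### The compulsion models adjust summed seconds for exposure time recorded after TMS instead of analysing the compulsion rate the protocol defines; if TMS changes exposure time, the arm coefficient loses its meaning as the TMS effect

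*Protocol article*

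**What the plan says.** Under Statistical methods {20a}, the Phase 1 section on compulsion duration defines the analysed variable: "EPCS-rated duration of observed compulsions (in seconds, summed across all sessions) will quantify compulsive behavior". Linear regression compares each active regimen with sham, and "total exposure duration (in seconds) will be a covariate in the model". The reason given is that exposure time varies, "relates to ERP outcomes, and can influence compulsion duration", because a longer exposure leaves more room for compulsions.

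The Phase 2 section on compulsion duration, a primary outcome there, carries this over to the group comparison and to the model for percent change in C/YBOCS: "Total exposure duration will be a covariate in both analyses".

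Elsewhere the outcome is a rate. Objectives {7} picks the regimen with the lowest compulsion rate if both pass, Outcomes {12} defines a rate per session for both phases, and Sample size {14} gives detectable effects for compulsion rate.

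On timing, Intervention description {11a} states: "Treatment sessions 2–11 will involve TMS immediately followed by ERP".

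On coding, the adherence section {11c} says "All ERP sessions will be video recorded and 100% will be coded using the Exposure Process Coding System", while the EPCS section says "study coders will code 80% of video-taped session data".

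**The concern.** Total exposure duration is not a baseline variable. It accumulates over sessions in which TMS has just been given, and TMS is intended to change how participants behave during exposure. Severity or avoidance could plausibly drive both exposure time and compulsions. Conditioning on such a variable can break the comparison that randomisation set up.

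The stated rationale, opportunity for compulsions, is an argument for analysing a rate. A free additive covariate does not produce one, so the analysis departs from the outcome named in three other sections. In the C/YBOCS model the opportunity rationale does not apply to the dependent variable at all, and the covariate can absorb part of the TMS effect.

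At stake are a Phase 2 primary analysis and the behavioural mediation model. Any bias could go in either direction and would not shrink with more participants. The conflicting coded shares add a further uncertainty about what the sum covers.

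**Working it through.** **The plan's own figures.** With 10% attrition, two-sided alpha 0.05 (assumed) and 80% power, a two-sample t-test with 27 per arm detects d = 0.777 (stated 0.78; power at 0.78 is 0.803). For Phase 1, a 2-df F test in 36 participants gives η² = 0.227 (stated 0.23). The sample-size figures are not in dispute. The 0.78 corresponds to an unadjusted comparison of two groups, not to the covariate model.

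**What the arm coefficient estimates.** Let A be arm, U an unmeasured shared cause, E exposure time (within-arm SD 1) and C compulsions:

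- E = δA + λU + error
- C = τA + βE + λU + error

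The direct effect is τ and the total effect is τ + βδ. Within arm, the slope of λU on E is λ². Regressing C on A and E therefore gives an arm coefficient of τ − λ²δ. It misses the direct effect by −λ²δ and the total effect by −(λ² + β)δ.

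The values β = 0.5, λ = 0 or 0.5, and δ = 0, 0.3 or 0.5 SD are assumptions; none is in the document.

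| δ | λ | Miss vs direct | Miss vs total |
|---|---|---|---|
| 0 | 0 or 0.5 | 0 | 0 |
| 0.3 | 0 | 0 | −0.5 × 0.3 = −0.15 |
| 0.5 | 0 | 0 | −0.5 × 0.5 = −0.25 |
| 0.3 | 0.5 | −0.25 × 0.3 = −0.075 | −0.75 × 0.3 = −0.225 |
| 0.5 | 0.5 | −0.25 × 0.5 = −0.125 | −0.75 × 0.5 = −0.375 |

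Negative δ reverses the signs. Simulation with 27 per arm and 4,000 replicates agrees (for example −0.076 and −0.125 against direct). With τ = 0 and λ = 0.5, rejection is 6% at δ = ±0.3 and about 9% at ±0.5, against about 5% with no shift. With τ = −0.5 and λ = 0.5, the estimate runs from −0.63 to −0.38 and rejection from 75% to 35%, against 59% with no shift.

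**Multiplicative version.** Here exposure is log-normal, TMS has no effect on the proportion of exposure time spent in compulsions, and there are 27 to 30 per arm. A 0.2 log shift means exposures about 22% longer (e^0.2 = 1.22) or 18% shorter (e^−0.2 = 0.82). All settings are assumed.

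| Setting | Covariate model rejects |
|---|---|
| No shift, or no shared cause | about 5% |
| Shift 0.2, correlation 0.5, log-exposure SD 0.2 | 42–44% |
| Same, SD 0.35 | 10–12% |
| Same, SD 0.4 | 16% |
| Same, shared cause explains only part of the proportion, SD 0.2 / 0.4 | 12–14% / 7–8% |
| Shift 0.2, correlation 0.8, SD 0.35 | 21–26% |
| Shift 0.4, correlation 0.5 / 0.8, SD 0.35 | 22–27% / 57–62% |

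The SD 0.35 rows come from a separate simulation with milder assumptions, so the rows are not one ordered series. Together with the linear check, the range at correlation 0.5 is roughly 6% to 44%; its lower end comes from the linear check, where the shift was 0.3 SD rather than 0.2 log units.

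**The ratio under other assumptions.** Compulsion seconds divided by exposure seconds rejected in 4–6% of trials in the SD 0.35 settings above. If compulsion seconds do not depend on exposure time or arm, the ratio rejects in 14–19% at a 0.2 shift and 47–61% at 0.4. If they grow with the square root of exposure, it rejects in about 10–11% and 26–28%. The covariate model stays at 4–5% in both cases.

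**Coded share.** Sessions 2–11 are 10 sessions. Coding 80% leaves 8, so a sum over equal sessions falls by 1 − 8/10 = 20%. If the share is the same in every arm, this only rescales the contrast in seconds and adds noise.

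**The case against.** The strongest reply is that the bias needs two conditions the article does not establish: TMS must change exposure time, and an unmeasured cause must link exposure time to compulsions. The article says only that exposure time varies naturally and relates to outcome, which describes a prognostic covariate. Therapists follow one manual and are masked to active versus sham. This stands, and it makes the point conditional. A reader might infer that the planned model will distort the TMS effect, or that the false-positive rate is known to be high; the document supports neither.

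Second, the ratio also uses exposure time, and it holds its level when the null is defined on the proportion because that null is built for it. This stands too. Neither analysis dominates, and the choice between them is a choice of estimand. What favours the rate is that the protocol already names one.

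Third, adjusting for opportunity has a reason: raw seconds with no allowance for exposure would depend on how many sessions were attended. That supports allowing for exposure in the compulsion outcome. It does not support exposure time as a covariate for C/YBOCS change once the mediator is itself a rate.

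Fourth, a reader might infer that coding 80% biases the arm comparison. Video coders are masked, so it would do so only if the uncoded sessions differed by arm. The 80% might also be one staff grade's share, but nobody is named for the remainder, so the two statements still conflict.

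**Conclusion.** The point holds in conditional form. The analysed variable does not match the stated rate, and the model conditions on a variable measured after randomisation and after TMS. If TMS leaves exposure time unchanged, there is no bias. If TMS changes it, the arm coefficient is not the total effect, and with a shared cause it is not the direct effect either. The size cannot be fixed from the document: in the linear illustration the miss against the total effect is 0.15 to 0.38 SD in either direction, and the false-rejection range above widens further with stronger correlation or a larger shift.

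The coding conflict is real but secondary. A reader might also infer that regimen selection is biased by the covariate. Objectives {7} refers to the lowest rate and does not say that it is read from this regression, so that step is not established. The matter is worth correcting before Phase 2 because it concerns a primary outcome and the correction is cheap.

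**What to change.** - Define the compulsion outcome once, as compulsion seconds per coded exposure second, and use it in Objectives, Outcomes, Sample size and both analysis sections. The present rate per session does not say whether counts or seconds are meant.
- Compare it by randomised arm, adjusting only for baseline variables (site and baseline C/YBOCS), with numerator and denominator taken over the same coded sessions.
- Remove exposure duration from the Phase 2 C/YBOCS model, and report exposure duration by arm.
- Keep the covariate-adjusted summed-seconds model and an unadjusted model as sensitivity analyses.
- Reconcile 100% with 80%. If 80% is right, select the coded sessions by one rule blind to arm.

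The cost is wording; no new data are needed. The downside is that the rate assumes compulsions scale with exposure time. It can mislead if they do not and TMS shifts exposure, so exposure by arm must be read beside it. A rule for very short exposure totals is also needed.

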### Other outcomes

We will explore group differences on secondary measures of clinical functioning listed in Table 1.

#### Phase 2

##### Primary outcome (connectivity in targeted circuit)

Following procedures outlined for this outcome in Phase 1, a two-sample *t*-test will assess the difference in RSFC in the targeted circuit pre- and post-treatment for active rTMS vs sham. A linear regression model will also be used with the outcome of interest being the percent change in OCD symptom severity (C/YBOCS) pre- and post-treatment. The primary predictor will be a group indicator for sham vs active TMS. Differences pre- and post-treatment in RSFC and its interaction with the group indicator will be included as potential mediators for the dependent variable.

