Primary outcomes focus on neural change and will be indexed by within-subject (pre- to post-treatment) and between-subject (iTBS vs. sham; cTBS vs. sham) change in fMRI-measured RSFC between the targeted network (pSMA-DLS for cTBS arm, dlPFC-DMS for iTBS arm). We will also examine several other outcomes. First, we will evaluate between-subject differences in compulsions during ERP (rate per session as observed by independent raters using EPCS). We will assess safety at baseline, post-treatment, daily treatment sessions, and 1-month follow-ups using the staff-administered Adverse Events Questionnaire (TMS AEQ), aggregated as the number of treatment-related adverse events and tolerability ratings of side effects. We will assess feasibility at post-treatment, based on treatment completion rate (percent of participants completing ≥ 80% of treatment sessions).

#### Phase 2

The primary outcomes are neural change (RSFC in the targeted circuit as in Phase 1) and change in compulsion rate (rate per session as in Phase 1). These will be indexed by within-subject (pre- to post-treatment) and between-subject (active vs. sham) change. We will also examine whether changes in neural and behavioral outcomes mediate change in OCD symptom severity (percent change in C/YBOCS total score from pre- to post-treatment). Secondary analyses will examine (1) the relationship between pre-treatment clinical measures and OCD symptom change, and (2) subgroup effects in primary outcomes, and (3) durability of change in primary outcomes through 1-month follow-up.

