### Assignment of interventions: allocation

#### Sequence generation {16a}

Block randomization, stratified on site (Brown or UMN) and baseline OCD severity (C/YBOCS total < 32 vs. > = 32), will be performed using the blockrand package in R [37].

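### The Phase 2 mediation regressions model percent change in C/YBOCS with no baseline C/YBOCS term, so initial severity can confound the mediator tests

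*Protocol article*

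**What the plan says.** Outcomes {12}, Phase 2, defines symptom change for the mediation question as "percent change in C/YBOCS total score from pre- to post-treatment". The statistical methods for Phase 2 repeat this in two regressions.

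- **Connectivity model.** The dependent variable is "the outcome of interest being the percent change in OCD symptom severity (C/YBOCS) pre- and post-treatment". Treatment enters as the main regressor: "The primary predictor will be a group indicator for sham vs active TMS". The mediator terms follow: "Differences pre- and post-treatment in RSFC and its interaction with the group indicator will be included as potential mediators for the dependent variable".
- **Compulsion model.** The dependent variable is "the outcome of interest being the percent change in OCD symptom severity (C/YBOCS) pre- to post-treatment". Treatment group is again the main regressor, and the mediator terms are parallel: "Compulsion duration and its interaction with the group indicator will be included as potential mediators for the dependent variable". One covariate is named: "Total exposure duration will be a covariate in both analyses".

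Baseline C/YBOCS is in neither list. It is collected before treatment (Table 1), and Sequence generation {16a} stratifies randomisation on "baseline OCD severity (C/YBOCS total < 32 vs. > = 32").

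**The concern.** Two features combine. First, dividing by baseline makes the value of a point depend on where the participant started. Second, with no baseline term, any remaining dependence of percent change on initial severity stays in the residual.

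For the randomised group contrast this is at most a matter of precision. For the mediator it can be bias. RSFC change and compulsion duration are observed after randomisation and are not assigned. Sicker youth may plausibly show more compulsion time. If initial severity drives both the mediator and the residual in percent change, the regression can report a mediator effect that does not exist. Linking target engagement to symptom change is a stated aim of Phase 2, so that is the inference at risk.

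**Working it through.** **Inputs from the protocol.** 30 per group in Phase 2; 10% attrition, so 54 analysed, 27 per arm (Sample size {14}). Lowest eligible C/YBOCS 16; severity cut 32.

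**Assumed inputs.** The article gives no C/YBOCS SD, pre-post correlation or effect scale. Assumed: two-sided alpha 0.05; baseline mean 26, SD 5 (4 to 6 for group power), limited to 16-40; mean fall 40%, so post mean 26 × 0.6 = 15.6; post SD 8; pre-post correlation r from 0.3 to 0.7; mediator-baseline correlation 0.3.

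**1. The plan's own figures.** Noncentral t with 27 per arm gives a detectable d of 0.777 at 80% power (plan: 0.78). Noncentral F with N = 54 gives η² = 0.159-0.160 for two tested terms and 0.196 for four (plan: 0.16 to 0.20). Both reproduce. Neither uses a C/YBOCS SD, so this point does not change them.

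**2. Weight of one point.** 1/16 = 6.25%; 1/32 = 3.125%; ratio 2. The same point change counts twice as much at baseline 16 as at 32.

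**3. When percent change still depends on baseline.** With an additive model, the slope of post on baseline is r × 8/5. The fraction of the score remaining (post/baseline) changes per baseline point by about (slope − 0.60)/26 near the mean:

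| r | slope | change per baseline point |
|---|---|---|
| 0.3 | 0.48 | −0.12/26 = −0.5 percentage points |
| 0.5 | 0.80 | 0.20/26 = 0.8 |
| 0.7 | 1.12 | 0.52/26 = 2.0 |

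If effect and noise are proportional to baseline, the slope equals 0.60 and the dependence vanishes.

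**4. False-positive rate of the mediator term.** Simulation of the planned structure (group, mediator, interaction), no true mediator effect, 10,000 trials per row:

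| Scenario | Percent change, no baseline | Post score with baseline |
|---|---|---|
| Additive, r = 0.3 | 4.9% | 5.0% |
| Additive, r = 0.5 | 6.3% | 4.8% |
| Additive, r = 0.7 | 14.8% | 5.2% |
| Proportional | 4.8-5.1% | 5.0-5.1% |

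The pattern follows step 3. Other runs at r = 0.7 gave 9.5% and 13.4%, hence roughly 10-15%.

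**5. Power of the mediator term when it is unrelated to baseline.** Additive: 82%, 82% and 74% for percent change at r = 0.3, 0.5 and 0.7, against 83-84% adjusted. Proportional: 84% against 82-83%.

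**6. Power for the group effect.** Group-only comparison, 27 per arm, adjusted d = 0.78:

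| Scenario | Percent change | Baseline-adjusted post score | Loss in points |
|---|---|---|---|
| Additive, r = 0.2-0.3 | 77-79% | 79-80% | 0-1 |
| Additive, r = 0.5 | 76-77% | 79% | 2-3 |
| Additive, r = 0.6 | 73-74% | 79% | 4-6 |
| Additive, r = 0.7 | 65-69% | 78-79% | 9-13 |
| Proportional effect and noise | 80-81% | 77-79% | none; 1-2 better |

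Further proportional runs favoured percent change by 1.4 to 2.8 points (for example 78.8% against 76.3%). Type I error of the group test was about 5% in both analyses. Step 6 tests group alone; with the interaction in the planned models, the group coefficient is conditional on the mediator, so these figures are indicative only.

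**The case against.** The best defence is that percent change is the natural scale if benefit is proportional. It then treats mild and severe participants alike, leaves no residual dependence on baseline and is slightly more powerful. The article does not say which scale holds, so a general claim that percent change loses power would be wrong. That stands.

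It is also fair that covariates are often left to an analysis plan, which is not shown here. This stands only in part: the article fixes the outcome scale in three places, enumerates the predictors, and names exposure duration where a covariate was wanted.

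Stratification on severity limits gross imbalance between groups, though not within strata. It does not balance severity across levels of the mediator, which is where the bias arises.

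Four stronger readings are tempting and are not supported:
- **Milder participants have more leverage.** Leverage depends on the predictors, and rescaling the outcome does not alter it.
- **Weighting mild cases more is always a distortion.** It is one only if benefit is additive in points.
- **Phase 2 is underpowered as a result.** Its primary outcomes are RSFC and compulsions, and their power figures reproduce.
- **These are the only symptom comparisons.** Phase 2 Other outcomes separately explores group differences in C/YBOCS change at post-treatment and 1 month, without defining that change as a percentage. Only the mediator link is confined to these two regressions.

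**Conclusion.** The point holds as a modest, conditional weakness of the two mediation models. The omission of baseline C/YBOCS is plain from the listed terms. Its main consequence is possible confounding of the mediator by initial severity: a false-positive rate of roughly 10-15% instead of 5%, given a mediator-baseline correlation of 0.3, additive change and a pre-post correlation of 0.7. The inflation is small at 0.5, absent at 0.3, and absent if effects are proportional. The power consequence for the group effect runs from a gain of 1-3 points to a loss of about 13. All of these sizes rest on assumed inputs that the protocol neither confirms nor excludes. The case for change is that the adjusted model protects the mediator test in every scenario examined and gives up little where percent change does better.

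**What to change.** In both Phase 2 symptom regressions, make post-treatment C/YBOCS the dependent variable and add baseline C/YBOCS and site as covariates. Keep group, the mediator, its interaction with group and, in the compulsion model, total exposure duration. Report percent change as a descriptive or sensitivity measure, and align the definition in Outcomes {12}.

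No new data, visits or participants are needed. The cost is about two model degrees of freedom: with 54 analysed, residual degrees of freedom fall from 54 − 4 = 50 to 48 in the connectivity model and from 54 − 5 = 49 to 47 in the compulsion model. If effects are truly proportional, it also costs 1-3 points of power. Because a stated outcome definition changes, it should be made as a documented amendment before Phase 2 data are available.

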### Sample size {14}

Power analyses for our sample sizes (phase 1 = 60, phase 2 = 60), assuming an attrition rate of 10%, (phase 1 = 54, phase 2 = 54) were calculated. In Phase 1, we will have 80% power to detect medium-to-large effects for within- and between-subject changes in RSFC (Cohen’s d range 0.70 to 0.96) and for group differences in compulsion rate (η2 = 0.23). In Phase 2, we will have 80% power to detect medium-to-large effects for tests of group differences in RSFC and compulsion rate (Cohen’s *d* = 0.78) and for tests of RSFC and compulsion rate as mediators of OCD symptom change (η2 range = 0.16 to 0.20).

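### Phase 2 tests TMS on each mediator and the mediator on symptoms separately, labels an interaction term a mediator, and never joins the two steps; the stated mediation power covers the second step only.

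*Protocol article*

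**What the plan says.** The protocol article (Outcomes {12}, Phase 2) sets the question: "We will also examine whether changes in neural and behavioral outcomes mediate change in OCD symptom severity".

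Under Statistical methods {20a}, Phase 2, each of the two primary-outcome sections plans two analyses.

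- **Connectivity, step one:** "a two-sample *t*-test will assess the difference in RSFC in the targeted circuit pre- and post-treatment for active rTMS vs sham".
- **Connectivity, step two:** "A linear regression model will also be used with the outcome of interest being the percent change in OCD symptom severity (C/YBOCS) pre- and post-treatment". On its terms: "The primary predictor will be a group indicator for sham vs active TMS", and "Differences pre- and post-treatment in RSFC and its interaction with the group indicator will be included as potential mediators for the dependent variable".
- **Compulsion duration, step one:** "a linear regression model will assess whether compulsion duration differs by treatment group".
- **Compulsion duration, step two:** the same form of C/YBOCS regression, where "Compulsion duration and its interaction with the group indicator will be included as potential mediators for the dependent variable".

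Sample size {14} bases power on 54 participants in Phase 2. It claims 80% power for group differences at d = 0.78, and 80% power for the tests of RSFC and compulsion rate as mediators at η² between 0.16 and 0.20.

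**The concern.** A mediated effect has two links: treatment moves the mediator (path a), and the mediator moves the outcome given treatment (path b). The article tests a in one analysis and b in another. It attaches the word mediator to terms of the second analysis alone. One of those terms, group × mediator, asks whether the mediator-outcome slope differs by arm, which is moderation. Nothing in the article says how the two analyses combine into a statement about mediation.

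This matters more here than in most trials because both arms receive ERP. The Background links change in these circuits to ERP response, and links the reduction of compulsions during exposure to better outcome. On the protocol's own reasoning, a mediator-outcome association is expected in both arms even if TMS leaves the mediator unchanged. Connecting target engagement to symptom change is a stated Phase 2 aim, so a reader may take a significant regression term as the answer.

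**Working it through.** **Inputs.** From Sample size {14} and Trial design {8}: 54 analysed, 27 per arm; d = 0.78; η² = 0.16 to 0.20. Assumed: two-sided α = 0.05, which is not stated for these figures. The true mediator-outcome association is also assumed, because the article gives only a detectable value; partial R² is varied from 0.09 to 0.20.

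**1. Reproduce the group-difference figure.** Two-sample t, 52 df, noncentrality d√(n/2) = 0.78 × √13.5 = 2.87. Power is 80.3%, and the smallest d with 80% power is 0.777. The stated 0.78 reproduces.

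**2. Reproduce the mediator figure.** Regression F test, N = 54, f² = η²/(1 − η²), noncentrality N·f². The η² giving 80% power is:

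| Terms tested | η² |
|---|---|
| 1 | 0.131 |
| 2 | 0.159 |
| 3 | 0.179 |
| 4 | 0.196 |

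The stated range matches an ordinary F test of 2 to 4 regression terms. Path a does not enter it.

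**3. The regression when TMS does not move the mediator.** Simulation with 27 per arm: M = e₁ and Y = bM + e₂, with b² = R²/(1 − R²), no direct effect and no true interaction; 6,000 trials per row. Percentage significant at 0.05:

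| Partial R² | M coefficient, interaction model, 0/1 coding | M and interaction, 2-df F | M coefficient, no interaction | Planned group-to-mediator test | Both paths |
|---|---|---|---|---|---|
| 0.09 | 36 | 49 | 60 | 5 | 3 |
| 0.16 | 56–58 | 77 | 86 | 5 | 4 |
| 0.20 | 68 | 88 | 93 | 5 | 4 |

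Both paths means that the group-to-mediator test and the mediator coefficient without interaction are each significant. The range in the first column is the spread over repeat simulations. That column is lower because, under 0/1 coding, the coefficient is the slope in the sham arm alone (27 people).

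The last column is close to the product of its two parts: at R² 0.16, 0.048 × 0.859 = 0.041.

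**4. Power to show both paths at the protocol's own detectable effects.** With TMS shifting the mediator by 0.78 SD:

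- R² 0.16: path a 81.0%, path b 85.7%; product 0.810 × 0.857 = 0.694; simulated 69.1%.
- R² 0.20: path a 81.1%, path b 92.1%; product 0.811 × 0.921 = 0.747; simulated 74.4%.

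If path b is instead judged by the 2-df F test, the simulated figures are 62% and 70%. All are below 80%.

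**The case against.** A reader might infer that the plan never estimates the effect of TMS on the mediator. The article does not support that: the opening sentence of each Phase 2 primary-outcome section plans exactly that comparison. A reader might also infer that the trial will declare mediation whenever the regression term is significant. No section says so. The wording is potential mediators, and no decision rule is given in either direction. The 58% to 86% is therefore not the trial's false-positive rate. It describes one analysis read without its neighbour, under an assumed association and a particular coding. Requiring the planned t-test together with the mediator coefficient from the planned interaction model gives 2.3% (0/1 coding) or 3.6% (±0.5 coding).

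Three further points are fair.

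- The total effect of TMS on C/YBOCS is covered under Phase 2, Other outcomes.
- Including the interaction is legitimate. If Y = c′X + bM + hXM and TMS shifts M by a, the indirect effect under active treatment is a(b + h). Only the label is wrong. The article does not state coding or centring, so one cannot say that the group coefficient will be misread.
- An SAP that is not shown may name an estimator, and mediation is not the main Phase 2 objective.

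These points lower the severity but do not remove the point. The article does more than leave an estimator open. It states a method for the mediation question, twice, and that method answers a different question. It also gives a power figure for mediator tests that covers only path b.

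**Conclusion.** The point holds in limited form. Both links are tested, but separately. The analysis presented as mediation gives the mediator-outcome association and its moderation by group, and nothing shown joins it to the group-to-mediator test.

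If TMS does not move the mediator and partial R² is 0.16, the regression alone gives a significant mediator coefficient in about 58% to 86% of trials, against about 4% when both paths are required. These percentages rest on the assumed association, and at R² 0.09 they fall to about 36% to 60%.

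The power finding depends less on assumption, because it uses the protocol's own detectable effects and only α is assumed. The stated 80% applies to the outcome regression, and power to show both paths is about 69% to 74%. No Go/No-Go criterion and no primary group comparison is affected. Should fix.

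**What to change.** In both Phase 2 primary-outcome sections, for each mediator:

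- Combine the planned group-to-mediator model with the C/YBOCS model. Report the indirect effect with a bootstrap 95% confidence interval, computed within the planned multiple imputation.
- Describe the group × mediator term as allowing the slope to differ by arm, with the mediator centred, and stop calling it a mediator.
- Take the total TMS effect on C/YBOCS from the model without mediators, which the group comparison under Other outcomes already provides.

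In Sample size {14}, either say that η² 0.16 to 0.20 is the detectable size for the outcome-regression terms, or give the power for both paths as about 69% to 74% with d = 0.78 on the mediator.

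The cost is a few sentences and a few lines of code, with no new data. Phase 2 had not begun when the article was published. The one drawback is that the stated mediation power becomes less favourable.
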